**Evaluatie algehele ziekteactiviteit (onderzoeker)**

Beoordeling PsA door **onderzoeker**:

1 = erg goed

2 = goed

3 = redelijk

4 = slecht

5 = erg slecht

**APPENDIX 3 68-JOINT SCORE**

|  | **Right** | | **Left** | |
| --- | --- | --- | --- | --- |
|  | Pain | Swelling | Pain | Swelling |
| Shoulder |  |  |  |  |
| Elbow |  |  |  |  |
| Wrist |  |  |  |  |
| MCP-1 |  |  |  |  |
| MCP-2 |  |  |  |  |
| MCP-3 |  |  |  |  |
| MCP-4 |  |  |  |  |
| MCP-5 |  |  |  |  |
| IP-1 |  |  |  |  |
| PIP-2 |  |  |  |  |
| PIP-3 |  |  |  |  |
| PIP-4 |  |  |  |  |
| PIP-5 |  |  |  |  |
| DIP-2 |  |  |  |  |
| DIP-3 |  |  |  |  |
| DIP-4 |  |  |  |  |
| DIP-5 |  |  |  |  |
| Hip |  |  |  |  |
| Knee |  |  |  |  |
| Ankle |  |  |  |  |
| MTP-1 |  |  |  |  |
| MTP-2 |  |  |  |  |
| MTP-3 |  |  |  |  |
| MTP-4 |  |  |  |  |
| MTP-5 |  |  |  |  |
| IP-1 |  |  |  |  |
| PIP-2 |  |  |  |  |
| PIP-3 |  |  |  |  |
| PIP-4 |  |  |  |  |
| PIP-5 |  |  |  |  |
| DIP-2 |  |  |  |  |
| DIP-3 |  |  |  |  |
| DIP-4 |  |  |  |  |
| DIP-5 |  |  |  |  |
|  |  |  |  |  |
| TOTAL |  |  |  |  |

0 = no tenderness

1 = pain on pressure

2 = pain and winced

3 = winced and withdrew

9 = not done, not assessable

Initialen v.d onderzoeker I_I_I_I Datum I_I_I-I_I_I_I-I_I_I

*Dag Maand Jaar*

**APPENDIX 4**

Standard Operating Procedure (SOP) biopsy handling Date: 11-09-2002

### Author : [name]/ [name]

### Version : 2 ____________________________________________________

- The arthroscopist collects at least 24 samples for the different analysis procedures.

[figure not shown]

For each study, a detailed collection scheme is available in the study specific file.

- Each set of 6 samples is collected on a wet gauze (saline 0.9%) and directly processed by the technician.

- Cryotubes are labeled with a waterproof lumicolor the following way:

Patient ID (Bx…..),procedure (IHC,ISH,PCR, MA or EMSA), date of the arthroscopy.

- Tubes with formaline for pathology are available at the arthroscopy room (top drawer of the table) and labeled as follows:

Patient name

AMC number

Date

- Tubes for EM are stored in the +4°C room (G1-125) bottom shelf of “reuma corner” (or available at pathology) and labeld as follows:

Study

Bx number

AMC number

Arthroscopy number

- Tubes for “lyme”disease are stored at -20°C (reuma) outside G1-111 in the corridor (or available at bacteriology) and labeled as follows:

Patient name

AMC number

Date

- Tubes for TBC / bacterial culture are stored at +4°C room (G1-125) bottom shelf of “reuma corner” (or available at bacteriology) and labeled as follows:

Patient name

AMC number

Date

After the arthroscopy :

- **PA**-tubes are given to the nurse
- **EM**-tubes are stored in the rheumatology case in the corridor of G1-111.
- **Lyme disease**-tubes are taken to bacteriology with a form by us or the nurse
- **TBC / Culture**-tubes are taken to bacteriology with a form by us or the nurse
- **Step 1. for IHC and ISH**

[figure not shown]

1

[figure not shown]

2

[figure not shown]

3

- **Step 2.**

Put the synovial tissue samples for IHC (6x) together en bloc on the bottom of two moulds (1).

Fill the moulds completely with Tissue-Tek OCT after the synovial tissue samples have been grouped on the bottom of the moulds (2). It is critical that there is physical contact between different biopsy samples so that it can be analysed as one mega-section. Put the moulds in the labeled cryotubes and let the tissue-tek with the samples for about 2 minutes for complete embedding of the tissue at RT. Snap freeze the cryotubes + moulds in liquid nitrogen (3). Keep the cryotubes in liquid nitrogen for 1 minute, until the Tissue-tek medium in the moulds become white. Leave the cryotubes in liquid nitrogen until storage.

# Step 3.

Put the mould in a labeled cryotube and let the tissue-tek with the samples for about 2 minutes for complete embedding of the tissue at RT. Snap freeze the cryotube + mould in liquid nitrogen. Keep the cryotube in liquid nitrogen for 1 minute, until the Tissue-tek medium in the mould becomes white. Leave the cryotube in liquid nitrogen until storage.

- **Step 4.**

[figure not shown]

[figure not shown]
Put the samples for PCR, MA and EMSA directly in a labeled cryotube and freeze immediately in liquid nitrogen.

- **Step 5.**

Put the samples for routine histology (PA) directly in a tube filled with 3.6% formalin for fixation.

All samples should be stored in a liquid nitrogen container. Location of the samples is noted in the Remedy and Excel database.

**APPENDIX 5**

# PSORIASIS AREA AND SEVERITY INDEX (PASI)

| Erythema  Induration  Scaling | None | Mild | Moderate | Severe | Very severe |  |  |
| --- | --- | --- | --- | --- | --- | --- | --- |
| AREA % | 0 | 1-9 | 10-29 | 30-49 | 50-69 | 70-89 | 90-100 |
| SCORE | 0 | 1 | 2 | 3 | 4 | 5 | 6 |

**Erythema (E)**

0 = none

1 = light red

2 = red, but not deep red

3 = very red

4 = extremely red

**Induration (I) (elevation, thickness, infiltration)**

0 = none

1 = slight, but definite to touch

2 = easily palpable with rounded or sloped edges

3 = definitely elevated with hard sharp borders

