- The clinical severity of the affected joints during treatment will be evaluated at each visit using the following parameters:

-Tender joint count (see appendix)

- Swollen joint count (see appendix)

-Visual Analogue Scale (VAS) pain (see appendix)

-VAS disease activity (see appendix)

-CRP and ESR

-Health Assessment Questionnaire (see appendix)

-Physician’s Global Assessment of Disease (see appendix)

-Patient’s Global Assessment of Disease (see appendix)

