**Scaling (S)**

0 = none

1 = mainly fine scale, some lesions partially covered

2 = coarser thin scale, most lesions partially covered

3 = coarser thick scale, nearly all lesions covered, rough

4 = very thick scale, all lesions covered, very rough

| **PASI** | Head | Upper limbs | Trunk | Lower limbs |  |
| --- | --- | --- | --- | --- | --- |
| Area % |  |  |  |  |  |
| Erythema |  |  |  |  |  |
| Induration |  |  |  |  |  |
| Scaling |  |  |  |  |  |
| Sum (E+I+S) |  |  |  |  |  |
| Area(Score) |  |  |  |  |  |
| SumxArea |  |  |  |  |  |
| x | x0.1 | x0.2 | x0.3 | x0.4 |  |
| Total | + | + | + | + | = |

| Score of the biopsy site |  |
| --- | --- |
| Erythema | + |
| Induration | + |
| Scaling | + |
| Total | = |

Initials of the investigator: Date:

Reference List

3. Nash P, Clegg DO: **Psoriatic arthritis therapy: NSAIDs and traditional DMARDs.** *Ann Rheum Dis* 2005, **64 Suppl 2:** ii74-ii77.

6. Kupper TS: **Immunologic targets in psoriasis.** *N Engl J Med* 2003, **349:** 1987-1990.

7. Mease PJ: **Psoriatic arthritis therapy advances.** *Curr Opin Rheumatol* 2005, **17:** 426-432.

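### The PASI form in Appendix 5 gives induration no grade 4, against its own five-level header; the joint form does not say whether its total is a count or a graded score

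*Protocol*

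**What the plan says.** **PASI (Protocol, Appendix 5).** One header covers erythema, induration and scaling: "None | Mild | Moderate | Severe | Very severe". In the same table these five labels stand over the scores 0 to 4. The descriptor lists follow. Erythema ends at "4 = extremely red" and scaling at "4 = very thick scale, all lesions covered, very rough". Induration ends at "3 = definitely elevated with hard sharp borders". In each of four body regions the three grades are summed, multiplied by an area score of 0 to 6 and weighted "x0.1 | x0.2 | x0.3 | x0.4". A separate box, "Score of the biopsy site", adds the three grades without area or weight.

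**Joints (Protocol, Section 3, Secondary efficacy variables, and Appendix 3).** Section 3 lists "Tender joint count (see appendix") and, in the same way, a swollen joint count. The table of contents describes Appendix 3 as tender and swollen joint counts. The synopsis and the form's own title speak of a score. The form has pain and swelling columns for each side, a legend grading tenderness 0 to 3, the code "9 = not done, not assessable", and a TOTAL row. It does not say how the total is formed or how swelling is entered.

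**The concern.** A header with five levels, two item lists with five grades and a third with four cannot all be right. If raters work from the lists, the truncation falls on the plaques with the most room to improve. Statistical methods plans an ANCOVA for each endpoint with the baseline value as covariate, so a capped baseline affects both the change and the adjustment. Analysis cannot repair this: a grade that was never recorded cannot be recovered afterwards.

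The joint form raises a lesser question of definition. A number of tender joints and a sum of tenderness grades are different endpoints. The protocol uses a term for each and points both to one form that does not choose between them. Swelling entries made without a key may also differ between assessors.

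**Working it through.** **Inputs.** From Appendix 5: grades E, I and S; area score A from 0 to 6; weights 0.1, 0.2, 0.3 and 0.4, which sum to 1.0. From Appendix 3: the joint rows and the tenderness grades 0 to 3. From Section 3, Design, and the sample-size paragraph: 24 patients randomised 1:1.

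**The stated figure.** The only stated figure that can be recomputed here is the 68 joints. Rows per side: 3 + 5 + 1 + 4 + 4 + 3 + 5 + 1 + 4 + 4 = 34, and 34 × 2 = 68. The title reproduces. The protocol states no maximum for PASI or for the joint total.

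**PASI ceiling.** PASI = sum over regions of weight × (E + I + S) × A.
- Induration 0 to 4: 1.0 × (4 + 4 + 4) × 6 = 72.
- Induration as listed, 0 to 3: 1.0 × (4 + 3 + 4) × 6 = 66.
- Difference: 6 points, or 6/72 = 8.3%.
- Biopsy-site score: 4 + 4 + 4 = 12 against 4 + 3 + 4 = 11.

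**Loss for one patient.** Recording a true 4 as 3 removes weight × A in each affected region. With all four regions affected and equal area scores, the loss is 1.0 × A, so 1 to 6 points. With one region affected at A = 6, it is 0.6, 1.2, 1.8 or 2.4 points, depending on the region's weight. With no very severe induration it is zero.

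**Effect on change (assumed values).** Take A = 3 in all regions and E/I/S moving from 3/4/3 to 2/2/2.
- Full scale: 10 × 3 = 30 falls to 6 × 3 = 18, a drop of 12 points (40.0%).
- Baseline induration capped: 9 × 3 = 27 falls to 18, a drop of 9 points (33.3%).

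The 3 points lost by one such patient shift the mean change of an arm of 24/2 = 12 by 3/12 = 0.25 points.

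**Joint total.** As a count the maximum is 68; as a sum of grades it is 68 × 3 = 204. As an assumed example, take five joints at grade 1, three at grade 2, two at grade 3, two not assessable and 56 at 0. The count is 5 + 3 + 2 = 10. The sum of grades is 5 + 6 + 6 = 17.

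**The case against.** - **A line may have been lost when the PDF was read.** Symbols are missing elsewhere in the text, and the missing grade would be the last line of its list. This cannot be excluded. But the erythema and scaling lists beside it are complete, so an omission in the form is more likely. The remedy should be worded as add or confirm.
- **The header still offers a fifth level.** A reader might infer that very severe induration cannot be scored at all. The document does not support that, because a rater who goes by the header could enter 4. What stands is that the header gives no descriptor for that grade, so the form gives two different answers.
- **The joint form is ambiguous, not wrong.** A reader might infer that it yields false totals, with code 9 added in as severe tenderness. Nothing tells anyone to sum the grades or the code, which is plainly labelled as not assessable. A tender count can be read off as the joints graded 1 to 3. Nor can one say that the endpoint simply is a count, since the synopsis and the form title say score. How unassessable joints are handled in analysis is normally left to the SAP and is not raised here.
- **The effect is limited.** The gap of 72 against 66 needs maximal area and severity everywhere. The inclusion criteria admit patients with only a documented history of psoriasis and set no minimum PASI. The same form serves both blinded arms, so a cap would tend to dilute an effect rather than favour an arm. All of this stands and bears on severity; it does not remove the contradiction.

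**Conclusion.** The contradiction in Appendix 5 holds: induration is headed with five levels but described with four, while its two sister items have five. If raters follow the list, PASI is lowered by weight × area score in each region with very severe induration. The loss is at most 6 of 72 points in total and 1 of 12 on the biopsy-site score, and improvement from that grade is understated. The conclusion assumes that the missing line is absent from the form in use and that raters work from the descriptors. The protocol does not say how many patients would have very severe induration, so the effect on group means cannot be given beyond the illustration.

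The joint-form point is one of inconsistent terms, an undefined total and a missing swelling key. The documents do not show that any total is wrong. Both endpoints serve the secondary objective on clinical response. The primary variables are synovial immunohistochemistry, and no sample-size or significance-level figure depends on either form. The point is modest but worth correcting.

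**What to change.** **Appendix 5.** Check the source form. Add, or confirm, the descriptor for induration grade 4 so that all three items run 0 to 4 under the shared header.

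**Appendix 3 and the text.** State that the tender joint count is the number of joints graded 1 to 3 and that the swollen joint count is scored yes or no per joint. Print a swelling key. Note that code 9 means missing and stays out of the total. Use one term, count, in the synopsis, Section 3 and the form title.

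The cost is a few added lines and the reissue of two forms. Sample size, visits and the planned analysis are unchanged. The PASI correction has to be made before forms are completed, because an unrecorded grade cannot be restored. The tender count can still be derived later if joint-level grades are kept.

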**Scaling (S)**

0 = none

1 = mainly fine scale, some lesions partially covered

2 = coarser thin scale, most lesions partially covered

3 = coarser thick scale, nearly all lesions covered, rough

4 = very thick scale, all lesions covered, very rough

| **PASI** | Head | Upper limbs | Trunk | Lower limbs |  |
| --- | --- | --- | --- | --- | --- |
| Area % |  |  |  |  |  |
| Erythema |  |  |  |  |  |
| Induration |  |  |  |  |  |
| Scaling |  |  |  |  |  |
| Sum (E+I+S) |  |  |  |  |  |
| Area(Score) |  |  |  |  |  |
| SumxArea |  |  |  |  |  |
| x | x0.1 | x0.2 | x0.3 | x0.4 |  |
| Total | + | + | + | + | = |

| Score of the biopsy site |  |
| --- | --- |
| Erythema | + |
| Induration | + |
| Scaling | + |
| Total | = |

Initials of the investigator: Date:

Reference List

3. Nash P, Clegg DO: **Psoriatic arthritis therapy: NSAIDs and traditional DMARDs.** *Ann Rheum Dis* 2005, **64 Suppl 2:** ii74-ii77.

6. Kupper TS: **Immunologic targets in psoriasis.** *N Engl J Med* 2003, **349:** 1987-1990.

7. Mease PJ: **Psoriatic arthritis therapy advances.** *Curr Opin Rheumatol* 2005, **17:** 426-432.

